**Results:**

This study received approval from the Research Ethics Committee in Universiti Putra Malaysia (JKEUPM-2023-1446) and Universiti Kebangsaan Malaysia (JEP-2024-669). The clinical trial was also registered in Australian New Zealand Clinical Trial Registry (ACTRN1264000243516). As of June 2024, the recruitment process is ongoing and a total of 48 and 49 students have been enrolled from the universities into the CBT-I and ISHE groups, respectively. All the participants provided signed and informed consent to participate in the study. Data collection has been completed for the baseline (pre-treatment assessment), and follow-up assessments for T1 and T2 for all the participants in both groups, while T3 and T4 assessments will be completed by July 2025. Data analysis will be performed by August 2025 and the research will be completed by December 2025.

**Conclusions:**

This study is the first attempt to design a CBT intervention to ameliorate poor sleep quality and its related negative effects among medical students. This research is also the first large-scale exploring the relationship between health status and CBT-mediated sleep improvement among medical students.

**Trial Registration:**

Australian New Zealand Clinical Trials Registry ACTRN12624000243516; https://www.anzctr.org.au/Trial/Registration/TrialReview.aspx?id=387030

**International Registered Report Identifier (IRRID):**

PRR1-10.2196/59288

## Introduction

### Background

It is scientifically acknowledged that sleep and executive functions undergo changes in prefrontal circuits that underlie executive functioning as part of healthy aging [1]. According to the model proposed by Harrison and Horne [2] and recent findings, selective sleep loss affects prefrontal cortex (PFC) circuitry, leading to changes in brain metabolism and impairing executive function in healthy adults [3-5]. Based on these findings, several studies have debated the vulnerability of the PFC to sleep loss [6,7]. A study investigating sleep problems and executive function among university students found a significant relationship between poor sleep quality (SQ) and impaired executive function [8]. Medical students, in particular, are frequently affected by poor SQ during their time in medical school [9].

Medical students from various countries have shown differing prevalence rates of poor SQ, including 44.2% in Nepal, 41% in Iran, 51% in the United States [10], 59% in Lithuania [11], 90% in China, 70.0% in Hong Kong, 32.5% in Nigeria, 37% in Saudi Arabia [12], and 62.0% in Ethiopia [13]. Recently, in Malaysia, a prevalence of 59.6% was reported among clinical students at International Islamic University Malaysia [14].

Sleep-related problems can result in substantial medical costs and human burden [15,16]. Sleep disorders such as insomnia affect approximately 25 million people in the United States annually, contributing to an estimated health care cost of US $100 billion [17]. Therefore, improving SQ among medical students through nonpharmacological interventions may help prevent or minimize the consequences of poor sleep, such as burnout.

To date, only a few effective nonpharmacological interventions are known to treat sleep-related issues such as poor SQ [18]. In a systematic review of nonpharmacological interventions aimed at improving sleep among university students (including 11% of medical students), cognitive behavioral therapy (CBT) accounted for 33.3% of the interventions, followed by sleep hygiene at 33.1%; relaxation, mindfulness, and hypnotherapy at 22.2%; and Gestalt therapy or imagery rehearsal therapy at 11.1%. The researchers concluded that CBT was effective in treating sleep disorders among university students. Additionally, other outcome variables, such as sleep duration, SQ, sleep onset latency (SOL), sleep hygiene, and dysfunctional beliefs about sleep, were examined [19]. Based on these findings, CBT and sleep hygiene education (SHE) were identified as the most commonly used interventions to improve SQ.

CBT for insomnia (CBT-I) is a nonpharmacological intervention recommended as the first line of treatment for improving SQ [20] and is considered the gold standard for insomnia treatment [21,22]. CBT-I was developed based on the Spielman behavioral model of insomnia [23] and is an extension of the stimulus control theory of insomnia [24]. It is a multicomponent psychotherapy, comprising elements such as sleep education, stimulus control therapy, sleep restriction therapy, cognitive therapy, sleep hygiene, and relaxation training [25,26].

CBT-I focuses on dysfunctional cognition and maladaptive behaviors that contribute to sleep problems. However, access to CBT-I is limited due to the shortage of trained personnel and the high cost of treatment [27-30]. Internet-based CBT-I (ICBT-I), with or without therapist guidance, has been successfully used for managing chronic insomnia [27,28]. Similarly, SHE has been reported to be equally effective in improving SQ among individuals aged 12 years and older [29]. However, SHE is a single educational intervention that focuses on sleep hygiene, whereas CBT-I is a multicomponent intervention. Therefore, CBT-I is considered a potentially more effective intervention for improving SQ and executive function among individuals, but evidence-based data to support this claim are lacking. Furthermore, studies comparing the effectiveness of CBT-I and SHE interventions are scarce. Despite recognizing SQ as a foundation of a healthy lifestyle, there is limited emphasis on sleep hygiene and sleep education in medical schools. Hence, this study protocol outlines the methodology of a randomized controlled trial (RCT) designed to examine the effectiveness of CBT-I and SHE on SQ and executive function among medical students. The secondary outcomes to be investigated include presleep worry, attitudes toward sleep, sleep hygiene, and sleep parameters.

### Conceptual Framework

This study will use several theories, namely, the cognitive models of insomnia, the hyperarousal models of insomnia, and the PFC circuitry model, to develop the theoretical framework for the interventions to be investigated. First, according to the cognitive model of insomnia (Figure 1), individuals with sleep problems often experience excessive worry, which prevents them from falling asleep and consequently leads to poor SQ [30]. As a result of this worry, individuals with sleep problems tend to focus on sleep-related internal threats (eg, bodily sensations) and external threats (eg, environmental noises). This selective focus causes them to become hyperaware of minor cues (previously unnoticed), which leads to excessive worry and anxiety. Additionally, individuals with sleep problems develop negative cognitions that further increase their cognitive and arousal activity, preventing them from falling asleep [30]. The model also suggests that individuals with sleep problems often engage in safety behaviors, such as napping or consuming alcohol, to relieve this arousal. However, these safety behaviors eventually worsen the worry and prevent individuals from challenging their negative sleep beliefs [30].

**Figure 1 figure1:**
[figure not shown]
The cognitive model of insomnia.

Second, the hyperarousal model of insomnia incorporates both the cognitive and behavioral models of insomnia, while integrating principles of classical conditioning [24,25]. This model posits that conditioned arousal is a key factor in perpetuating sleep problems. It further explains that repeated associations between poor sleep and the bed can increase conditioned arousal, with the bed and sleep environment becoming stimuli for heightened arousal [31]. Cognitively, individuals with increased sleep arousal begin to perceive “learned sleep–preventing associations,” thereby perpetuating their sleep problems [25].

Third, it is scientifically acknowledged that sleep and executive functions undergo alterations in prefrontal circuits that support executive function as part of healthy aging [1]. According to the model proposed by Harrison and Horne [2] and recent findings [3-5], selective sleep loss affects PFC circuitry, potentially leading to changes in brain metabolism that impact executive function in healthy adults. Building on these findings, several studies have debated the vulnerability of the PFC to sleep loss [6,7]. In this study, improvements in SQ may affect the PFC circuitry, particularly executive function. Consistent with this, our study aims to use ICBT-I to alleviate poor SQ and enhance executive function among medical students. The delivery of ICBT-I overcomes common limitations associated with traditional face-to-face administration, such as the lack of trained personnel, high costs, and limited treatment availability due to time constraints [30].

### Research Aim and Hypotheses

This study aims to elucidate the effects of improved SQ on executive function. The following hypotheses will be investigated in the trial:

ICBT-I will lead to a significant improvement in SQ compared with the SHE intervention at 1 month (T2), 3 months (T3), and 6 months (T4) postintervention.ICBT-I will lead to a significant improvement in executive functioning compared with the SHE intervention at 1 month (T2), 3 months (T3), and 6 months (T4) postintervention.ICBT-I will lead to a significant improvement in total sleep time (TST), SOL, number of awakenings (NOA), wake time after sleep onset (WASO), and sleep efficiency (SE) compared with the SHE intervention at 1 month (T2), 3 months (T3), and 6 months (T4) postintervention.Dysfunctional beliefs, attitudes about sleep, presleep worry, and sleep hygiene will significantly mediate the between-group differences in study outcomes at 1 month (T2), 3 months (T3), and 6 months (T4) postintervention.

## Methods

### Trial Design

A 2-arm, parallel-group RCT will be conducted, comparing ICBT-I with internet-delivered SHE (ISHE). The trial design is summarized in Figure 2. The study population will consist of preclinical medical students who meet the established criteria for poor SQ, as indicated by self-report assessments, which are internationally recognized as standardized instruments. The medical students will be randomly assigned in a 1:1 ratio to either the ISHE or ICBT-I group. All interventions will be conducted online using a paid Zoom (Zoom Video Communications/Qumu Corporation) platform. As shown in Figure 2, participants will receive an electronic document containing the participant information statement, screening instruments, informed consent form, and randomized allocation to the intervention groups. Both baseline and follow-up assessments will be conducted either online or via mobile platforms. Participants will be able to print the participant information statement, and contact details (phone numbers and emails) will be provided for participants to reach the researchers before consenting and during the data collection process.

**Figure 2 figure2:**
[figure not shown]
The trial design. dTMT: Digital Trail Making Test; ICBT-I: internet-based cognitive behavioral therapy for insomnia; ISHE: internet-based sleep hygiene education; PSQI: Pittsburgh Sleep Quality Index; UKM: Universiti Kebangsaan Malaysia; UPM: Universiti Putra Malaysia.

### Ethics and Dissemination

Ethical approval for this study was obtained from the Human Ethics Committees at Universiti Putra Malaysia (UPM; JKEUPM-2023-1446) and Universiti Kebangsaan Malaysia (UKM; JEP-2024-669). Informed consent will be obtained from each potential participant before their recruitment into the study. They will be briefed on their right to participate or decline, as well as their right to opt out of the study without penalty. Regarding privacy and confidentiality, data will be fully anonymized, and no detailed information about participants will be recorded. No incentives will be provided for participation in this study.

The RCT protocol aligns with the SPIRIT (Standard Protocol Items for Randomized Trials) guidelines [32], as shown in the recruitment and assessment procedures in Figure 2. The uploaded SPIRIT checklist can be found in Multimedia Appendix 1. Multimedia Appendix 2 presents the protocol approval obtained from the Australian New Zealand Clinical Trials Registry (ANZCTR; ACTRN12624000243516). Upon completion of the study, all data will be stored in the institutional database for a specified duration before being destroyed. The findings will be published as a research article in a journal, with no information that could reveal the participants’ identities.

### Sample Size Estimation

As shown in Figure 3, the sample size for the RCT was calculated using G*Power software (Heinrich-Heine-Universität Düsseldorf), selecting the *F* tests for analysis of variance: repeated measures, within-between interaction. The calculation was based on a precision level of 0.05, a study power of 95%, an effect size of 0.20, and a correlation coefficient of 0.5 among the outcome measures. Therefore, the minimum required sample size for each group is 56. A low effect size of 0.20 was chosen based on previous interventions addressing SQ [33]. After adjusting for a 10% dropout rate, the sample size was increased to 60 medical students per group. Given that this is a 2-arm RCT, a total of 120 medical students will be required to complete the study.

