### Assessment Points

Participants in both groups will be assessed at baseline (week 0 or pretreatment assessment), week 6, 1 month, 3 months, and 6 months after the intervention. T0 represents the pretreatment assessment, while the subsequent 4 assessment points are designated as T1, T2, T3, and T4, respectively.

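### The printed inputs give a total of 56 for the planned four-measurement analysis, not 56 per group, and an f of 0.20 in this routine is not a low between-arm effect

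*Protocol article*

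**What the plan says.** The Sample Size Estimation section of the protocol article describes a G*Power calculation, "selecting the *F* tests for analysis of variance: repeated measures, within-between interaction". It gives these inputs: "The calculation was based on a precision level of 0.05", followed by "a study power of 95%, an effect size of 0.20, and a correlation coefficient of 0.5 among the outcome measures". The result is stated as "Therefore, the minimum required sample size for each group is 56". The effect size is justified in these words: "A low effect size of 0.20 was chosen based on previous interventions addressing SQ". An allowance for dropout then takes the figure to 60 per group and 120 in total.

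The text of that section gives neither the number of measurements nor the sphericity correction. Figure 3, which is captioned as the G*Power calculation, is not shown in the copy reviewed. Elsewhere, Assessment Points sets a baseline (T0), and "the subsequent 4 assessment points are designated as T1, T2, T3, and T4, respectively", which makes five assessments. Data Analysis plans the repeated measures ANOVA on T0, T1, T2 and T3, which makes four.

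**The concern.** The sample size that this routine reports is the total across groups. If the total was copied as a per-group number, the stated size does not follow from the stated inputs, and the stated power of 95% does not belong to the stated size.

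The label *low* adds a second problem. A reader will tend to take a low effect of 0.20 as a small standardised difference between arms. The routine takes 0.20 as an interaction f, which corresponds to a much larger gap between arms. The paragraph then reads as a promise of 95% power for a small benefit. The comparator is active and shares sleep hygiene, psychoeducation and relaxation content with the intervention, so a modest difference or a null result is quite possible. A null result could be misread as ruling out small benefits.

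**Working it through.** **Inputs.** From Sample Size Estimation: within-between interaction F test, alpha 0.05, power 0.95, f = 0.20, correlation rho = 0.5. From Trial Design: k = 2 groups, 1:1. The number of measurements m is not stated there, so it is varied from 2 to 5. Epsilon is not stated in the text; it is taken as 1, the default, and varied below.

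**Formula.** With N the total sample size:
- noncentrality: lambda = f² × N × m × epsilon / (1 − rho)
- df1 = (k − 1)(m − 1) × epsilon
- df2 = (N − k)(m − 1) × epsilon
- power = probability that a noncentral F(df1, df2, lambda) exceeds the 5% critical value.

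**Step 1: reproduce the figure.** Smallest even total N with power of at least 0.95, at epsilon 1:

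| m | Total N | Power at that N | Power at N − 2 | Power at N = 112 |
|---|---|---|---|---|
| 2 | 84 | 0.952 | 0.947 | 0.987 |
| 3 | 66 | 0.950 | 0.944 | 0.998 |
| 4 | 56 | 0.954 | 0.946 | 0.9997 |
| 5 | 48 | 0.952 | 0.942 | >0.9999 |

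For m = 4 and N = 56: lambda = 0.04 × 56 × 4 / 0.5 = 17.92, df1 = 3, df2 = 54 × 3 = 162, power 0.954. For m = 4 and N = 112: lambda = 35.84, df2 = 330, power 0.9997. A simulation of 5,000 trials with m = 4 gave 0.958 at N = 56 and 0.999 at N = 112. The stated 56 per group (112 in total) is therefore not reproduced, but 56 as a total for four measurements is.

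**Step 2: what f = 0.20 means between arms.** Take equal arms at baseline and a constant gap of d SD at every later measurement. The interaction f is half the standard deviation over time of the gap (0, d, …, d), that is f = (d/2) × √(m − 1) / m.
- m = 4: f = (d/2) × 0.4330 = 0.2165d, so f = 0.20 gives d = 0.20 / 0.2165 = 0.92 SD.
- m = 5: f = (d/2) × 0.40 = 0.20d, so f = 0.20 gives d = 1.00 SD.

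Other patterns with no gap at baseline change the number, but for m = 2 to 5 none brings the largest gap below 0.80 SD.

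**Step 3: if 0.20 was meant as a sustained standardised difference.** Then f = 0.2165 × 0.20 = 0.0433 (m = 4) or 0.20 × 0.20 = 0.04 (m = 5). Power at N = 120 is 0.175 or 0.165, about 17%.

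**Step 4: what 120 delivers.** After 10% dropout, 120 × 0.90 = 108 are evaluable. With rho = 0.5, epsilon 1 and a constant gap after baseline:

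| m | 95% power | 80% power |
|---|---|---|
| 4 | f = 0.142, d ≈ 0.66 SD | f = 0.113, d ≈ 0.52 SD |
| 5 | f = 0.132, d ≈ 0.66 SD | f = 0.106, d ≈ 0.53 SD |

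**Step 5: vary what is not printed.** m = 3 with epsilon 0.5 gives a total of exactly 112. For m = 4, epsilon 0.40 gives 108 and 0.35 gives 120. For m = 5, epsilon 0.35 gives 104 and 0.30 gives 116; epsilon 0.80 gives 56. Setting rho to 0 with m = 4 gives 110, but the section states 0.5. Two other effect-size scalings give 146 to 148 (m = 4) or 118 to 120 (m = 5), and neither uses the stated correlation.

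**The case against.** The strongest reply is that the calculation cannot be declared wrong while Figure 3 is not shown. The number of measurements, epsilon and the effect-size option are not printed, and three measurements with epsilon 0.5 do give 112. This part stands: it cannot be said that no setting yields 56 per group. It does not rescue the text, because such a low epsilon is not mentioned and three measurements fit neither the four-point analysis nor the five-point schedule.

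It also follows that reading a total as a per-group number is an inference, not a demonstrated fact. Five measurements with epsilon 0.80 also give a total of 56.

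A reader might infer that the calculation used four measurements where it should have used five. The document does not support that as an error in this section: Data Analysis specifies the ANOVA on T0 to T3. Whether T4 belongs in that analysis is a separate matter.

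A reader might also infer that 0.20 is simply a large effect. On the generic f scale it lies between small and medium. It becomes large only when translated into a gap between arms, and the translation depends on the assumed pattern of means. Which scale the authors had in mind cannot be settled, since the cited source is not available here.

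Finally, the slip runs in the cautious direction: on the stated inputs it doubles the trial. That stands too.

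**Conclusion.** The sample size paragraph is wrong as written. With the named routine, the printed inputs and epsilon 1, the total is 56 for the planned four-measurement analysis and 48 for five, against a stated 112. The 95% figure fails on either reading of 0.20: power is over 99.9% at 112 if it is an interaction f (4 or 5 measurements), and about 17% at 120 if it is a sustained standardised difference. The word *low* misleads because f = 0.20 corresponds to about 0.92 SD (m = 4) or 1.0 SD (m = 5) between arms under a constant gap after baseline.

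A reader might go further and conclude that the trial is too small. The document does not support that: for the effect size the routine was given, 120 is more than enough. What is unsupported is the impression of 95% power for a small effect.

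These figures assume equal correlations of 0.5, epsilon 1 and, for the SD conversions, equal arms at baseline with a constant difference afterwards.

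**What to change.** Keep 120 participants and rewrite the paragraph to:
- state that the inputs give a total of 56 for the four-measurement analysis (48 for five), and that 120 exceeds this;
- state the number of measurements and the epsilon used, consistent with the Data Analysis section;
- replace *low* with the effect on a named scale (interaction f, with the between-arm difference in SD that it implies);
- state what the trial can detect: with 108 evaluable after 10% dropout, correlation 0.5, epsilon 1 and a constant post-baseline difference, 95% power for about 0.66 SD and 80% for about 0.52 SD (0.66 and 0.53 SD with five measurements);
- state that a null result does not exclude smaller effects.

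The cost is one paragraph and a less favourable statement of the detectable effect. No participants are added, and the allocation and analysis are unchanged. The correction should be made before the results are interpreted.

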### Randomization and Allocation Concealment

As participants will be recruited from 2 different universities, a stratified randomization method will be used to ensure balance between the groups from each university. Eligible students will be grouped by university and gender before random selection. Gender will serve as a matching factor during the stratified randomization process to ensure a comparable number of female and male students are recruited from both universities.

Data will be collected from volunteer medical students, and the researchers will have no influence on the randomization process or access to future allocations. Each participant will be assigned an identification number and listed before being randomized into either the ISHE or ICBT-I group using online randomization software [34]. A total of 60 students will be allocated to each group.

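### Sixty per group does not follow from the stated minimum of 56 and 10% dropout: it leaves 54 per group, 2 below that minimum (a minor inconsistency, not a shown loss of power)

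*Protocol article*

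**What the plan says.** The Sample Size Estimation section of the protocol article uses G*Power with the F test for "repeated measures, within-between interaction". Its inputs are given as follows: "The calculation was based on a precision level of 0.05", with "a study power of 95%, an effect size of 0.20, and a correlation coefficient of 0.5 among the outcome measures". From these it concludes that "the minimum required sample size for each group is 56". The next step is "After adjusting for a 10% dropout rate, the sample size was increased to 60 medical students per group", and the section closes by saying that "a total of 120 medical students will be required to complete the study".

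Randomization and Allocation Concealment states: "A total of 60 students will be allocated to each group". The abstract and Participants and Recruitment also use 120 as the target. Sixty per group is therefore the number randomised, before any dropout.

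**The concern.** Three figures in consecutive sentences do not fit together: a minimum of 56 per group, a 10% dropout rate, and 60 per group as the adjusted size. If 56 is the number needed for analysis, 60 is too few to protect it at the dropout the plan itself expects.

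The closing sentence blurs the matter further. Read literally, it makes 120 the number who must finish, which would leave no room for dropout because 120 is also the number allocated. A reader of the results could then compare the final number of completers with 56, 60 or 120 and find some support in the text for each. At stake is whether the sample-size statement can be checked and whether the trial can be said to have met its own target.

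**Working it through.** **Inputs.** From Sample Size Estimation: minimum 56 per group, dropout 10%, adjusted size 60 per group, alpha 0.05, power 95%, effect size 0.20, correlation 0.5. From Trial Design: two arms, 1:1. The number of measurements (m) entered in G*Power is not in the text, and Figure 3 is not available here. Data Analysis names T0 to T3 (four points), while Assessment Points schedules T0 to T4 (five). I therefore take m from 2 to 5.

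**Step 1: the dropout adjustment.**
- Standard inflation, n/(1 − d): 56/0.90 = 62.2, so 63 per group, 126 in total.
- Shortcut, n × (1 + d): 56 × 1.10 = 61.6, so 62 per group, 124 in total.
- Neither gives 60. A base of 54 would (54/0.90 = 60), but the text says 56.

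**Step 2: what 60 per group delivers.**
- Expected completers: 60 × 0.90 = 54 per group, 108 in total.
- Shortfall against the printed minimum: 56 − 54 = 2 per group; 112 − 108 = 4 in total.
- Dropout covered: 1 − 56/60 = 6.7%.

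**Step 3: can 56 be reproduced, and what is the power at 108?** Assumptions: 0.20 is Cohen f under G*Power's default definition for this test, and sphericity holds (epsilon = 1). For total N and 2 groups, the noncentrality is λ = N f² m/(1 − ρ), with df1 = m − 1 and df2 = (N − 2)(m − 1). With f² = 0.04 and 1 − ρ = 0.5:

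| m | Total N for 95% power | λ at N = 108 | Power at N = 108 | Power at N = 112 |
|---|---|---|---|---|
| 2 | 84 | 17.28 | 0.985 | 0.987 |
| 3 | 66 | 25.92 | 0.997 | 0.998 |
| 4 | 56 | 34.56 | 0.9995 | 0.9997 |
| 5 | 48 | 43.20 | 0.9999 | >0.9999 |

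The plan's 56 appears exactly once, as the total for four measurements (28 per group). No m from 2 to 5 gives 56 per group. In every row 108 exceeds the total needed for 95% power, and the change from 112 to 108 is at most about 0.003.

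**Step 4: sensitivity.** A sphericity correction of 0.5 with m = 3 does require a total of 112, which is 56 per group, and 108 would then fall just short of 95%. The article states no such correction. G*Power's alternative effect-size definition requires totals of 330, 198, 148 and 120 for m = 2 to 5. It matches neither 56 nor 112, and it does not use the correlation that the article lists as an input.

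**The case against.** The sponsor can say, with reason, that the gap is only 2 per arm, that the 10% is itself a planning guess, and that on the stated inputs nothing measurable is lost between 112 and 108. If 56 is really the total, each arm needs only 28, and 60 per arm would tolerate 1 − 28/60 = 53.3% dropout. The closing sentence can also be read as the number needed to carry the study out, since every other section treats 120 as the number recruited and allocated. All of this stands as to consequence. None of it makes 60 the result of adjusting 56 for 10% dropout, and no other section removes the conflict.

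In the other direction, a reader might infer that the trial fails to deliver its planned 95% power. The document does not support that: the shortfall is against a printed minimum that does not itself reproduce as a per-group figure, and the stated inputs give power above 95% at 108. Nor do the six-month follow-up and the absence of incentives show that dropout will exceed 10%.

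**Conclusion.** The point holds as a minor internal inconsistency. The stated minimum and dropout rate imply 63 per group (62 by the shortcut). The 60 stated and allocated leaves 54, which is 2 below the minimum, and covers 6.7% dropout instead of 10%. This part rests on the article's own figures alone.

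A loss of power is not shown. That part rests on reading 0.20 as Cohen f under the default definition, correlation 0.5, alpha 0.05, epsilon = 1 and 2 to 5 measurements, which give about 0.985 to above 0.999 at 108. The more useful question is whether 56 is a per-group figure or a total. The match at four measurements suggests a total but does not prove it, because the number of measurements entered is not in the text. The use of 120 as a completion figure is mainly a matter of wording.

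**What to change.** Four edits within Sample Size Estimation, with no change to enrolment:

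1. Replace the dropout sentence with: *120 students randomised (60 per arm); with 10% dropout, 54 per arm (108 in total) are expected to be evaluable.*
2. Recheck the G*Power output and state whether 56 is the number per group or the total.
3. Quote the power for 108 evaluable students, together with the number of measurements, the effect-size definition and any sphericity correction used.
4. In the last sentence, describe 120 as the number to be randomised.

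The cost is a few sentences and one rerun of the calculation. The stated evaluable number becomes slightly smaller than the text now implies; the design and the analysis are unaffected.
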